## Abstract

**Background:**

Despite the existence of evidence-based therapy options for the treatment of chronic pain and comorbid depressive symptoms (e.g., CBT), many individuals remain untreated. Treatment gaps result from a lack of specialists, patient fear of stigmatization, or patient immobility. Internet-based self-help interventions could serve as an anonymous and flexible alternative treatment option. In a pilot study, chronic pain patients with comorbid depressive symptoms who used a generic Internet-based depression program showed a significant reduction in depressive symptoms (but not pain symptoms) compared to a waitlist control group. Based on these findings, we developed the low-threshold, anonymous, and cost-free Internet-based self-help intervention Lenio that is tailored to the specific needs of chronic pain patients with comorbid depressive symptoms. Lenio is accompanied by the smartphone application (app) COGITO designed to increase therapeutic success. With Lenio and COGITO addressing both chronic pain and depressive symptoms, the trial aims to increase treatment effects of online interventions for chronic pain patients by reducing both depressive symptoms and pain.

**Methods:**

The effectiveness of the Internet-based self-help intervention and accompanying smartphone app will be evaluated in a randomized controlled trial (RCT). A total of 300 participants will be randomized into an intervention group (Lenio/COGITO), an active control group (depression-focused smartphone app), or a waitlist control group. Assessments will be done at baseline, after an 8-week intervention period (post), and after 16 weeks (follow-up). The primary outcome is the post-assessment reduction in “pain impairment” (mean value of impairment in daily life, free time, and work) as assessed by the DSF (German pain questionnaire).

Secondary outcomes will include the reduction in depressive symptoms as well as in the severity of pain.

**Discussion:**

Lenio is one of the first Internet-based interventions to reduce chronic pain and depression that will be empirically evaluated. Internet-based interventions could offer a promising alternative to conventional face-to-face psychotherapy in the treatment of chronic pain patients. The primary objective of the current study is to add essential insight into the feasibility, effectiveness, and acceptance of Internet-based interventions for people with chronic pain and depressive symptoms.

**Trial registration:**

DRKS-ID DRKS00026722, Registered on October 6th, 2021.

## Introduction

### Background and rationale {6a}

#### The interaction of pain and emotional well-being

Pain is a psychophysiological warning sign that protects us from potential danger [36]. However, pain, especially when it manifests as a chronic condition, may become a profound problem for the affected individual. Worldwide, chronic pain is among the most common causes for seeking medical care, with a global prevalence of 15% to 45% and estimated economic costs in the US at $600 billion annually [49, 54]. Research findings highlight the negative effects of chronic pain on quality of life [10] in both private and professional life [16]. Considering these findings, it is not surprising that up to 75% of chronic pain patients experience comorbid depressive symptoms [32].

The relationship between chronic pain and depressive symptoms is likely bidirectional. On the one hand, depression can contribute to the multifactorial genesis of chronic pain [47], while on the other hand depressive symptoms can emerge as a result of impairments in psychosocial functioning and low quality of life due to chronic pain [44].

#### Psychotherapeutic treatment of pain

The gate control theory was the first model to emphasize the role of psychological factors on the experience of chronic pain, and its development initiated the integration of psychological strategies in the treatment of chronic pain [37]. Multiple studies found significant improvements in chronic pain and depression scores after psychotherapeutic interventions [22, 48, 55]. A meta-analysis by Veehof and colleagues [52] reported significant improvements in chronic pain intensity, and chronic pain interference at medium effect sizes after acceptance- and mindfulness-based interventions compared to wait-list, medical treatment-as-usual, as well as educational and support control groups. Although effective psychotherapeutic treatments like this are available, many individuals remain untreated. Psychological and social influences on the genesis and maintenance of chronic pain are often not recognized or addressed in standard pain treatment [38]. Furthermore, a significant amount of affected individuals experience (self-)stigmatization, which often accompanies depressive symptoms and is detrimental to patients’ motivation to seek psychotherapeutic treatment [11]. Moreover, immobility among pain patients may make traveling to healthcare institutions difficult [13, 18]. As a result, there is a need for low-threshold, easily accessible, and anonymous support services to help overcome the treatment gap of individuals with both chronic pain and depressive symptoms.

#### Internet-based psychological interventions

Internet-based psychological interventions present an alternative to conventional face-to-face psychotherapy in the treatment of chronic pain patients [8, 30, 48]. In recent years, many studies have replicated the effectiveness of Internet-based interventions for numerous mental disorders [8, 30, 48]. Firstly, Internet-based interventions are resource efficient and safe [21]. Secondly, due to flexibility in timing, intensity, and focus as well as anonymity and privacy, compliance with Internet-based programs is high [26, 25].

Internet-based interventions can be implemented as unguided (self-help) or guided treatment (individual support by a therapist, such as by telephone). According to a meta-analysis, guided Internet-based interventions have a similar effectiveness to conventional face-to-face therapy [8]. Most studies show greater effect sizes for guided than for unguided Internet-based interventions [46]. However, unguided Internet-based interventions are superior in terms of cost and resource efficiency as well as anonymity [25]. Their main drawback, adherence, may be counteracted by e-mail reminders and by presenting information in textual rather than non-textual format [1].

#### Internet-based psychological interventions for chronic pain

A recent systematic review of online interventions targeted at chronic pain found a small to moderate effect on pain intensity reduction (Hedges' *g* =  − 0.33) [6]. Programs that address both chronic pain and depressive symptoms are rare and randomized controlled trials (RCTs) examining their short- and long-term efficacy in large samples are scarce. To the best of our knowledge, there is no open-source Internet-based self-help program for the treatment of chronic pain and comorbid depressive symptoms.

Miegel and colleagues [39] evaluated an unguided Internet-based intervention named Novego for the treatment of depression in a sample of chronic pain patients. Significant reductions with small to moderate effect sizes in depressive symptoms in the Novego group were found compared to a wait-list control group (η_p_^2^ = 0.043). However, reductions in pain intensity compared to the wait-list control group were only observed for a small subgroup (e.g., pain localization in the upper back or hands). Hence, an Internet-based program specifically tailored to the individual needs of chronic pain patients with comorbid depressive symptoms, rather than depressive symptoms only, could augment these effects.

To provide a low-threshold, anonymous, and open-source Internet-based self-help intervention for chronic pain patients with comorbid depressive symptoms, we developed Lenio as part of the current research project. Lenio is a novel Internet-based self-help intervention addressing both chronic pain and depression. It is to be used in combination with a smartphone application (app) called COGITO (uke.de/cogito). Research has shown that the combination of Internet-based programs and smartphone apps that transfer psychotherapeutic strategies into everyday life may increase therapeutic success as well as adherence [51]. Previous RCTs of a pilot version of the COGITO app found significant reductions in self-reported depressive symptoms and an increase in self-esteem among those who used the app regularly compared to wait-list controls [5, 33].

### Objectives {7}

The aim of the current research project is to investigate the feasibility, effectiveness, and acceptance of the Internet-based self-help intervention Lenio in combination with the smartphone app COGITO in an RCT. As the primary objective, a significant reduction in pain impairment (mean value of impairment in daily life, leisure time, and work; primary outcome) as measured by the German Pain Questionnaire (German acronym: DSF) in the intervention group compared to a waitlist and an active control group is expected. Furthermore, we also assume that depressive symptoms, as well as pain-related cognitive biases (e.g., catastrophizing, fear-avoidance beliefs), will be significantly reduced in the intervention group compared to the two control groups. Hence, the treatment of a highly prevalent condition could be improved.

### Trial design {8}

The self-guided Internet-based intervention Lenio will be evaluated in the framework of a randomized controlled trial (RCT). Participants will be randomly allocated (ratio 1:1:1) to one of three conditions: (1) intervention group (direct access to the Internet-based intervention Lenio and the smartphone app COGITO), (2) waitlist control group, or (3) active control group (access to a transdiagnostic smartphone app named MCT & More).

The waitlist control will show the effect of the intervention against no treatment, while the active control will show the effect of the intervention versus an Internet-based intervention addressing psychological problems but not chronic pain {6b}.

## Methods: participants, interventions, and outcomes

### Study setting {9}

Data will be collected online at baseline, post intervention (8 weeks after baseline), and follow-up (16 weeks after baseline). The online surveys will be generated using the software Qualtrics®, which meets standards of data safety regulations. Both the waitlist control group and the active control group will receive access to the Internet-based programs Lenio and COGITO after completion of the follow-up assessment 16 weeks after baseline.

### Who will take informed consent? {26a}

At the online baseline survey, participants will be informed about the aims and the procedure of the study, inclusion and exclusion criteria, and their right to withdraw from study participation at any time. Subjects may request deletion of data already collected pending data evaluation.

### Data management {19}

All participants will be instructed to create an e-mail address without personally identifiable information. No additional personal data (e.g., names, addresses) will be collected. All e-mail addresses will be treated confidentially, will not be passed on to third parties outside of the research team, and will be deleted after the study’s end.

### Participant timeline {13}

After giving informed consent, sociodemographic and psychopathological data will be assessed. At the end of baseline, individuals will be randomized equally to one of the three conditions. Randomization will be conducted automatically in Qualtrics®, preventing influence by third parties {16a}. At post-intervention and follow-up, psychopathological data, subjective evaluation, and side effects will be examined. For participating in each of the three online surveys (baseline, post, follow-up), participants will receive €10 Amazon® vouchers (as much as €30 total) as an incentive.

Instructions after baseline will be delivered via e-mail. The intervention group will receive their login details for Lenio and COGITO. One week later, individuals in the intervention group who do not log into Lenio will receive a reminder, including an overview of the program. Adherence will be further enhanced by sending e-mails that include descriptions (including tips) of specific modules. The active control group will receive instructions and an MCT & More download link for Android and IOS. Both the active control and the waitlist control group will receive log-in details for Lenio after completion of the follow-up survey 16 weeks after baseline.

Links to the post and follow-up assessments will be sent by automatically triggered e-mails. If participants will have not participated in a particular survey, they will receive a maximum of two e-mail reminders at intervals of 1 week. (The first e-mail reminder will be automated. However, the second reminder will be a personal message from the principal study investigator) {18b} (Table 1).

**Table 1 Tab1:**
[figure not shown]
This table is based on the SPIRIT (Standard Protocol Items: Recommendation for Interventional Trials) timeline. BDI-II, Beck Depression Inventory-II; CEQ, Credibility/Expectancy Questionnaire; DSF, German Pain Questionnaire; FABQ, Fear-Avoidance Beliefs Questionnaire; PSEQ, Pain Self-Efficacy Questionnaire; IEQ, Injustice Experience Questionnaire; PCS, Pain Catastrophizing Scale; PHQ-9, Patient Health Questionnaire-9; URICA, University of Rhode Island Change Assessment Scale; WHQOL-BREF, World Health Organization Quality of Life abbreviated version; WSQ, Web Screening Questionnaire

### Sample size {14}

The sample size calculation was conducted using G*Power®. Given that Miegel and colleagues [39] examining the effect of an unguided Internet-based interventions for depression on chronic pain patients found small to moderate effects, a moderate effect in the current study can be expected [39]. For analysis of covariance, the software yielded a required sample size of 246 with an expected effect size of η_p_^2^ = 0.06 (moderate effect), an alpha of 0.05 (two-sided), and a power of 0.95. We expect a drop-out rate of 25%. Hence, we aim to recruit 300 participants in total, with 100 participants per condition.

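### Recruiting 300 with the plan's own 25% drop-out leaves 225 participants, not the required 246, so the stated power of 0.95 is not met

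*Protocol article*

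**What the plan says.** All the figures stand together in the protocol article, Sample size {14}. For an analysis of covariance with a partial eta squared of 0.06, "an alpha of 0.05 (two-sided), and a power of 0.95", "the software yielded a required sample size of 246". The section then continues: "We expect a drop-out rate of 25%. Hence, we aim to recruit 300 participants in total, with 100 participants per condition".

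Other sections show what the 300 refers to:

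- The abstract (Methods) says "A total of 300 participants will be randomized into an intervention group", so 300 is the number randomised and not the number screened.
- Trial design {8} gives three arms: "Participants will be randomly allocated (ratio 1:1:1) to one of three conditions".
- Participant timeline {13} places randomisation at the end of the baseline survey, and Eligibility criteria {10} has exclusions settled at baseline. Losses from the 300 therefore occur after randomisation.
- Statistical methods {20a} names ANCOVA with the baseline score as covariate.
- The section on non-adherence and missing data {20c} plans an intention-to-treat analysis with multiple imputation, and a per-protocol analysis limited to people who completed the post-assessment.

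**The concern.** The section links three numbers as a chain: 246 needed, 25% lost, therefore 300 recruited. A reader will take this to mean that 300 recruits deliver 246 analysable participants, and with them a power of 0.95, after the expected losses. One multiplication shows that they do not.

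The issue is what the trial may claim later. If the primary comparison is null, the stated power is what readers will use to judge how informative that result is. A results paper that repeated the claim of 95% power after allowing for 25% drop-out would be repeating something the plan's own inputs contradict. No estimate or test is biased by it. The sample-size justification is simply wrong as written.

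**Working it through.** **Inputs.** From Sample size {14}: partial eta squared 0.06, alpha 0.05, power 0.95, required N 246, drop-out 25%, target 300 (100 per arm). From Trial design {8}: three equal arms. From Statistical methods {20a}: baseline score as covariate. The article does not print the numerator degrees of freedom or the number of covariates entered in the software. I assume the omnibus three-group test (numerator df = 2) and one covariate.

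**Step 1: reproduce 246.** Power comes from the noncentral F distribution:

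- f² = 0.06/(1 − 0.06) = 0.0638, so f = 0.2526
- noncentrality λ = N × f²
- df1 = 3 − 1 = 2; df2 = N − 3 − 1 = N − 4

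The smallest N with power of at least 0.95 is 245, and the next multiple of three is 246 (82 per arm). At N = 246, λ = 15.70, df2 = 242 and power is 0.951. The plan's figure is reproduced, so 246 is plain software output with no drop-out allowance inside it. Other entries fit less well: rounding f to 0.25 gives 251, and a one-degree-of-freedom test gives 206.

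**Step 2: apply the drop-out.**

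| Calculation | Result |
|---|---|
| Participants left from 300 after 25% loss: 300 × 0.75 | 225 (75 per arm) |
| Shortfall: 246 − 225 | 21, or 21/246 = 8.5% |
| Recruits needed for 246 after 25% loss: 246/0.75 | 328 (330 with equal arms) |
| Common but incorrect inflation: 246 × 1.25 | 307.5, so 308 |
| Drop-out that 300 can absorb: 1 − 246/300 | 18% |

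Neither the correct inflation nor the common mistaken one gives 300.

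**Step 3: effect on power** (same test, partial eta squared 0.06).

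| N with post data | λ | df2 | Power | Type II error |
|---|---|---|---|---|
| 300 (no loss) | 19.15 | 296 | 0.980 | 2.0% |
| 246 (18% loss) | 15.70 | 242 | 0.951 | 4.9% |
| 225 (25% loss) | 14.36 | 221 | 0.931 | 6.9% |

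With f rounded to 0.25, power is 0.947 at 246 and 0.926 at 225. The drop is again about two points, so the size of the effect does not depend on that choice.

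**The case against.** The arithmetic is not in dispute. The case on the other side is that it matters little and that 0.93 is less certain than it looks. Four points deserve weight.

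- **The loss is about two points.** Power of 0.93 is still high, and a null result would be read almost the same way. This stands, and it limits the practical weight of the finding. It does not make the derivation correct.
- **Drop-out is not tied to a time point.** If the 25% means loss by the 16-week follow-up, more than 225 could have 8-week data. This is possible. But the primary outcome is at the post-assessment, and a drop-out allowance in a sample-size calculation is naturally read as loss to that outcome. The 225 should be stated as conditional on that reading.
- **Multiple imputation keeps all 300 in the intention-to-treat set.** The survey links are sent separately, so someone who misses the post survey may still answer at follow-up, and some information could be recovered. Someone lost at both times contributes mainly baseline data, and the baseline score is already the covariate. Intention-to-treat power therefore lies somewhere between 0.931 and 0.980. Nothing in the article shows that imputation makes good 21 missing outcomes, and the sample-size section does not rely on it. The per-protocol set is limited to 225 at most.
- **The figure is for the omnibus test, whereas the objective compares Lenio with each control.** This is correct, and the figure must be labelled accordingly. As an illustration, suppose the two controls are equal and Lenio differs from both. Then the standardised difference is d = 3f/√2 = 0.536. A single unadjusted pairwise comparison (normal approximation) has power of about 0.929 with 82 per arm and 0.907 with 75 per arm, which is also a loss of about two points.

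**Conclusion.** The concern holds. The target of 300 does not follow from 246 and a 25% drop-out, and no other section reconciles the three figures. At the plan's own drop-out rate the expected number with post data is 225, and complete-case omnibus power is about 0.93, not 0.95.

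The error in the derivation is certain, because it needs only the numbers printed in one section. The 0.93 rests on three assumptions: the omnibus three-group test with one covariate (which reproduces 246), the whole 25% being lost by the 8-week post-assessment, and no information gained from imputation. The practical consequence is minor. This is an inconsistent drop-out allowance with a small loss of power, not a seriously underpowered trial.

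**What to change.** Current study status says that recruitment is complete, so the remedy is to correct the text and not to enrol more participants. Replace the last two sentences of Sample size {14} with wording such as:

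> *We randomise 300 participants (100 per condition). If 25% do not provide the post-assessment, about 225 contribute observed primary outcome data, which gives a complete-case power of about 0.93 for the three-group ANCOVA test at a partial eta squared of 0.06. The planned power of 0.95 (246 participants) is preserved for a drop-out of up to 18%.*

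It would also help to state the software entries (numerator degrees of freedom and number of covariates), so that a reader can reproduce 246 and see that the power refers to the omnibus test. The results paper should carry the corrected figures.

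The cost is a short text correction and a slightly less favourable power statement. The design, the analysis and the number randomised do not change.

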### Recruitment {15}

Participants will be recruited in inpatient and outpatient clinics and institutions that will inform potential participants about the study and distribute the study flyers. Flyers will include study information and a QR code that leads directly to the baseline survey. Furthermore, study information and links will be distributed in Facebook groups regarding relevant topics (e.g., self-help groups for chronic pain). In addition, a Facebook/Instagram and Google Ads campaign has already been set up. The campaign targeted different groups of pain patients (e.g., pain caused by accidental injury). Further sources of recruitment are through self-help groups, Internet forums, websites and newsletters of health insurance companies/associations, and various social media platforms (Instagram, Reddit, Twitter, YouTube, LinkedIn), which is especially helpful in reaching people from the community and not only patients that are already in treatment.

### Eligibility criteria {10}

For inclusion in the RCT, participants must meet the following criteria:Presence of depressive symptoms (Beck Depression Inventory-II (BDI-II) score ≥ 14; Patient Health Questionnaire-9 (PHQ-9) score ≥ 10),Chronic pain symptoms (mean score pain intensity on the German Pain Questionnaire (DSF) ≥ 4),Aged 18 to 75 years,Informed consent,Sufficient knowledge of the German language,Willingness to participate in three anonymous online surveys,Willingness to use the Internet-based treatment program over a period of 8 weeks minimum, andAccess to a computer/laptop and a smartphone.

The program has been developed for a heterogeneous target group of chronic pain patients with comorbid depressive symptoms. No formal diagnosis (of chronic pain and/or depressive symptoms) is needed as symptoms will be assessed by validated questionnaires at baseline. Effects of prior diagnoses as well as concurrent treatment programs will be analyzed in moderation analyses (see statistical analyses).

Exclusion criteria are a lifetime diagnosis of a schizophrenia spectrum disorder, bipolar disorder, substance abuse disorder, or acute suicidality (assessed by one item on suicidality on the Web Screening Questionnaire; WSQ).

Inclusion and exclusion criteria will be assessed at baseline. Excluded participants will be forwarded to an additional survey page providing the reason for exclusion and a contact e-mail address of the principal study investigator. In case of exclusion due to acute suicidality, participants will also be provided with phone numbers of crisis services.

